## Methods/Design

The study design consists of a nationwide case control study. The projected period of study are the 2010/2011 and 2011/2012 academic years. The study protocol has been revised and fully approved by the national research ethics committee ("Comité National d'Ethique de Recherche" CNER, approval N° 201009/07 version 1.1) and it has been notified to the national commission for data protection ("Commission Nationale pour la Protection des Données" CNPD).

### Case definition

In Luxembourg, the ministry operates a centralized management system for secondary education that allows identifying "school dropouts", i.e. students who leave school during the academic year or at year-end without any graduation. The definition applies for students who definitely left the educational system and have no specific occupation at all, but also for students who left school and began to work, or registered with an employment program. It also includes so-called "temporary" dropouts, who reregister with the educational system after some period of absenteeism (more than 3 months). For this research, temporary dropouts will be eligible as we tend to interview the student as soon as possible after he/she had dropped out.

### Control definition

The control group will be chosen from the same source and composed by students who are enrolled in regular secondary education and who attend classes. They will be individually matched for age, gender, school and educational grade.

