**Methods/Design:**

The objectives of this study are to investigate the type and prevalence of psychiatric disorders among school dropouts and to compare the findings with those by a matched control group of regularly enrolled students. Furthermore, family variables and socioeconomic status will be analysed, as they are factors likely to interfere with both educational attainment and mental health. A trained psychologist will use structured interviews and self-report forms to investigate for mental health issues, information on schooling, socioeconomic situation and family life. Controls will be matched for gender, age, school type and educational grade.

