Regarding the consensus for a multifactorial approach to psychiatric disorders, we consider it crucial to investigate for risk factors and protective factors derived from the individual and social domains as well as interactions among those factors. Socioeconomic status (SES) was reported to have an impact on both mental health [20] and educational attainment [21]. Indeed, among students with a low SES, 44% of school dropout could be attributed to psychiatric disorder, whereas the proportion increased to 61% for students with a high SES [22].

In the same way, family variables correlated with both mental health [23,24] and education [25,26]. In 1996, Bernstein and Borchardt analyzed different types of family composition in school refusal. They found out that communication and role behaviour seemed to be problematic in mother-only households [27]. According to Bernstein, difficulties in role behaviour may reflect symptoms of separation anxiety in children, who refuse to leave home because they worry about or care for a physically or emotionally vulnerable parent [23].

In the light of previous research, we hypothesize that school dropouts have significantly more mental health problems than their peers who go to school. They are also more likely to report a poor socioeconomic background, negative school experiences (repeating classes, disciplinary measures, absenteeism, problematic relations with authority and peers) and difficulties in family functioning (task fulfilment, role performance, communication, affective expression, connectedness, control behaviour, values and standards).

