### Research questions

The first objective of this research is to assess the type and prevalence of psychiatric disorders among early school leavers in Luxembourg and to compare the findings with those by a control group matched for gender, age, school and educational grade. If there is an association between mental illness and school dropout in Luxembourg, is it significant for only one psychiatric disorder or more (comorbid disorders)?

As a second objective, we aim to identify specific protective and risk factors derived from the individual and family domains by including school experiences, sociodemographic background and family variables (task fulfilment, role performance, communication, affective expression, connectedness, control behaviour and values and standards) in the analysis. These thematic analyses will establish which experiences are specific to school dropouts with mental health problems, which are specific to school dropouts without mental health problems, and which to students enrolled in regular secondary education.

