### Statistical analysis

To evaluate the representativeness of the school dropouts included in the study, a comparative analysis will be conducted on age, gender, educational grade, grade repetition, nationality, household composition and employment status.

Results will be expressed as mean and standard deviation (SD) for quantitative measurements and as frequency tables for categorical findings. The association between two continuous variables will be assessed by the correlation coefficient. Matched groups means values will be compared by two-way analysis of variance (or paired Student t-test) while the symmetry test (or McNemar Test) will be used for paired proportions. To identify variables associated with school dropout, we will conduct a conditional logistic regression analysis for matched pairs' data with school dropout as the outcome and psychiatric disorders, socioeconomic background and family variables as predictors of interest. The approach used to model psychiatric disorders within cases and controls with risk factors and/or prognostic factors will consist in a stepwise descending regression modeling technique starting from the full model in which all potentially and clinically important variables are included. Statistical control factors will concern demographic variables and school experiences. Comparison of embedded models will be done with the likelihood ratio test. Results will be considered as statistically significant at the 5% critical level (p < 0.05). All calculations will be carried out using the SAS^® ^System (Version 9.2 for Windows) statistical package and SPSSInc PASW Statistics 18.

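### Matching on both age and educational grade removes or weakens the case-control contrast on repeated classes that the plan hypothesises, and the article names two different school matching variables

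*Protocol article*

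**What the plan says.** The Control definition section sets the matching: "They will be individually matched for age, gender, school and educational grade". Research questions gives the same list, with "a control group matched for gender, age, school and educational grade". The Methods/Design paragraph of the Abstract differs in one variable: "Controls will be matched for gender, age, school type and educational grade". No age tolerance is stated.

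The last paragraph of the Background hypothesises that dropouts more often report "negative school experiences (repeating classes, disciplinary measures, absenteeism, problematic relations with authority and peers". Repeated classes are the first item in that list.

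Statistical analysis plans paired t-tests and McNemar tests, and then: "we will conduct a conditional logistic regression analysis for matched pairs' data with school dropout as the outcome". It adds: "Statistical control factors will concern demographic variables and school experiences". Grade repetition is named there only among the variables used to judge how representative the participating dropouts are.

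**The concern.** A student's age minus the usual age for the grade is the number of years behind, and repeated classes are a main reason for being behind. A control of the same age in the same grade is equally far behind. The plan thus predicts a difference between cases and controls in repetition, then selects controls in a way that makes the two groups alike on it. Paired methods draw information only from pairs that differ, so little or none is left. A finding of no difference could be produced by the matching alone, and a reader could wrongly take it as evidence that repetition is unrelated to dropout. Once controls are recruited, the lost contrast cannot be recovered from the pairs.

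The second matter is a plain contradiction. Students of the same school and students of any school of the same type are different control pools, and the ministry needs to know which one to draw the five candidates per case from.

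**Working it through.** **Inputs.** From the documents: the matching variables (Control definition, Research questions, Abstract), one control per case (Recruitment procedure), the paired analysis (Statistical analysis) and 146 per group (Sample size calculation), used here only as the number of pairs. The 146 does not follow from the stated odds ratio of 2.0 and prevalence of 13.7% (about 222 per group two-sided, 175 one-sided). That is a separate matter, and this point does not depend on it. The documents give no repetition or late-entry rates, so the following are assumptions: 30% of controls ever repeated, true odds ratio 2, a second repeat in 25% of repeaters, and late school entry in 0% to 30%, equally in cases and controls.

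**Repetition in cases.** 2 × 0.30 / (0.70 + 2 × 0.30) = 0.462.

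**No matching on age plus grade.** Discordant share = 0.462 × 0.70 + 0.30 × 0.538 = 0.323 + 0.162 = 0.485. Pairs: 146 × 0.485 = 71. Difference in percentages: 46.2 − 30.0 = 16.2 points.

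**Exact age and grade, no late entry.** Years behind equals years repeated, so both members of a pair have repeated or neither has. Discordant pairs: 0. The odds ratio cannot be estimated.

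**Exact age and grade, 10% late entry.** Pairs can differ only when both members are one year behind, one through repetition and the other through late entry.
- Cases one year behind: 0.462 × 0.75 × 0.90 + 0.538 × 0.10 = 0.365, of whom 85.3% repeated.
- Controls one year behind: 0.30 × 0.75 × 0.90 + 0.70 × 0.10 = 0.2725, of whom 74.3% repeated.
- Case only repeated: 0.365 × 0.853 × 0.257 = 0.080. Control only repeated: 0.365 × 0.147 × 0.743 = 0.040.
- Discordant pairs: 146 × 0.120 = about 17. Difference: 8.0 − 4.0 = 4.0 points, against 16.2.

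**Age tolerance of one year, no late entry.**
- Case only repeated: 0.462 × 0.75 × 0.70 = 0.242.
- Control only repeated: 0.538 × 0.225 / 0.925 = 0.131.
- Discordant pairs: 146 × 0.373 = about 54. Difference: 11.1 points.

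Simulation over the full range agrees:

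| Matching | Late entry | Discordant pairs of 146 | Matched odds ratio |
|---|---|---|---|
| Not on age plus grade | any | 71 | 2.0 |
| Exact age and grade | 0% | 0 | not estimable |
| Exact age and grade | 5% | 10 | 1.98 |
| Exact age and grade | 10% | 17 | 1.95 |
| Exact age and grade | 20% | 27 | 2.02 |
| Exact age and grade | 30% | 30 | 1.99 |
| Age within 1 year, same grade | 0% to 30% | 53 to 55 | 1.83 to 2.19 |

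**Precision.** The standard error of the log odds ratio is √(1/b + 1/c), where b and c are the two discordant counts. At an odds ratio of 2, the approximate 95% interval is 1.2 to 3.3 with 71 discordant pairs, 1.1 to 3.5 with 54, 0.9 to 4.3 with 30, and 0.5 to 7.4 with 10. In every exact-matching row, an odds ratio of 2 gives an interval that includes 1.

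**What the remaining pairs compare.** Under exact matching, they set a repeater against a student equally old for the grade for another reason. If late entry carries its own odds ratio for dropout, the matched value is the ratio of the two: 2 / 1 = 2 if late entry is harmless, and 2 / 2 = 1 if being over-age carries the same risk however it arose.

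**The case against.** The best reply is that the article states no age tolerance and may leave one to the full protocol. With one year of tolerance, about 53 to 55 discordant pairs remain of 71, and most of the contrast survives. This stands: it is why the point is that the contrast is removed or weakened, and not that the hypothesis can never be tested. It also stands that repetition is one item among several. Disciplinary measures, absenteeism and relations with authority and peers are not fixed by age and grade. The second objective's comparison of dropouts with and without mental health problems is made among cases, so the matching does not touch it.

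A reader might go further in four ways that the documents do not support.

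- **Part of the mental-disorder effect is matched away.** This requires disorder to act on dropout through repetition. The article neither states nor quantifies that path, and its Discussion says the sequence of events cannot be established. With an assumed direct odds ratio of 1.7, the crude value is 1.8 to 2.35 if the path exists and about 1.7 if it does not. If repetition is a confounder, matching on it is legitimate. The model already controls for school experiences, so a conditional effect may be what is intended.
- **The odds ratios for disorder, affluence and other school experiences are pulled toward 1.** Nothing shows this. Conditional regression respects the matching; fewer discordant pairs cost precision and do not by themselves cause bias.
- **The odds ratio for repetition itself must be biased toward 1.** The paired difference in percentages does shrink. The odds ratio stays near 2 in the calculations while late entry is unrelated to dropout, and moves toward 1 only if late entry raises the risk too.
- **Over-age cases will lack controls and be lost.** The article gives no school or grade sizes, and does not say that a case with fewer than five candidates is excluded.

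**Conclusion.** The point holds in limited form. Followed as written, matching on age and grade removes the within-pair contrast on repeated classes (exact age, no late entry) or weakens it (late entry or an age tolerance). On the assumed rates, discordant pairs fall from about 71 of 146 to 0, to 10 to 30, or to 53 to 55 respectively. The paired difference is pulled toward zero in each case. Any odds ratio that remains is imprecise under exact matching and compares repetition with other reasons for being over-age. A null result on repetition is therefore not interpretable. The mechanism follows from the text; the counts rest on assumed rates and show the range only.

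The conflict between school and school type is certain and needs no assumption.

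**What to change.** 1. Keep the matching. Remove repeated classes from the case-control hypotheses in the Background, or report them descriptively only.
2. State that the matched design cannot validly estimate the association of repetition with dropout, and that a null result on it is uninterpretable.
3. Describe the effect of mental disorder as conditional on age-for-grade.
4. Use one matching variable, school or school type, in the Abstract, Research questions, Control definition and the request to the ministry. The documents do not show which is intended; two of the three places say school.

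Items 1 to 3 cost only wording. Item 4 costs wording and one settled field in the data request, and should be done before controls are requested.

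Dropping grade from the matching is an option, not a required correction. It would restore the contrast on repetition, but controls could then be at a different educational stage from their cases, which may confound the first objective for the sake of one secondary item.

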### Inclusion criteria

Eligible participants are aged 16-25 years, residing in Luxembourg and enrolled in a national public secondary school. Since data will be collected in face-to-face interviews, participants must be reachable (students in acute hospitalization or under arrest are not eligible). They also need to understand either German or French, which are the languages of self-report questionnaires. An informed consent must be signed by the student and his/her legal guardian if he/she has not attained full age.

### Recruitment procedure

A request will be submitted to the ministry of education (MENFP) to get contact data of eligible participants. As shown in Figure 1, the recruitment procedure slightly differs for cases and controls.

**Figure 1 F1:**
[figure not shown]
**Stages of field research**. Figure 1 gives an overview of field research stages, beginning with the selection of eligible participants realised in collaboration with the ministry and "Action Locale pour Jeunes" (ALJ), their recruitment and finally the evaluation procedure, which consists of face-to-face interviews.

Figure 1: Stages of field research

The recruitment of school dropouts will be incident and realised in collaboration with a service operated by the ministry and called "Action Locale pour Jeunes" (ALJ). Every month, the ALJ receives a listing of all school dropouts who they contact in order to find out about their current occupation. If needed, they provide academic or vocational support.

As we expect a major denial of participation, all eligible dropouts listed in a monthly record will be systematically contacted.

A preliminary telephone contact provides information on the study (objectives, procedure, expected benefits) and asks for participation. If the student is interested in participating, an appointment for the interview is immediately set up and informed consent will be sent. It should be noted that information avoids deterrent terms such as "psychiatric" or "mental" and rather refers to "personal wellbeing". Meetings with cases will be organised in the regional offices of ALJ as we consider it an uncommitted, well accepted site.

The recruitment of controls will be subsequent to the participation of dropouts. There will be one control per dropout who participated in the study. Expecting a major denial of participation, we will ask the ministry to get a selection of 5 matched controls per case. Among these 5 controls, selection will be randomised.

The recruitment and evaluation procedures will be same than for cases (cf. Figure 1), but interviews will take place at school and outside of school hours.

### Sample size calculation

Considering an overall lack of prevalence rates of mental disorders in Luxembourg, we refer to the European Study of the Epidemiology of Mental Disorders [4] to assume a prevalence rate of 13.7% for any psychiatric disorder in the age group 18-24 years. Previous studies have reported a significant association between psychiatric disorders and subsequent school dropout by identifying odds ratios ranging from 1.0 to 5.7 depending on the disorder category [11,13,14]. To demonstrate that young adults with a psychiatric diagnosis compared with young adults without any psychiatric diagnosis have an odds ratio (OR) of at least 2.0 for dropping out of school, with alpha error set at 0.05 and statistical power of 80%, 146 participants per group will be needed.

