Between 2003 and 2006, the national authorities had to face dropout rates of more than 15%. As a result, they introduced accompanying and preventive measures to reduce linguistic and cultural risk factors that may impede educational engagement and vocational decisions. Since then, the dropout rate has overall declined. According to the latest figures, the national dropout rate, for the academic year 2008/2009, was set at 9% [2] and hence conceded with the European benchmark of no more than 10%. However the proportion of early school leavers who remain without any specific occupation is still alarming.

When questioned on their rationale for leaving school, students reported 1) difficulties in vocational guidance, 2) academic failure or the anticipation of failure, 3) a lack of incentive to pursue any formal education, 4) the lack of an apprenticeship, 5) personal reasons, or 6) health issues [2]. In the light of these statements, dropout prevention needs to consider what may underlie the reported difficulties, by examining factors relating to the student. Insight into the correlates that can influence alienation from school, and thus dropout, will be provided by exploring individual factors such as mental health, family life and socioeconomic situation.

Adolescence can be an unsettling period of life, marked by physical, psychological and social changes. It is known that up to 50% of lifetime mental disorders have their onset during adolescence [3] and that prevalence rates of at least one DSM IV disorder range from 13.7% [4] to 22.2% [5]. Such disorders include substance use, disruptive behaviour disorders, anxiety and mood disorders.

Nevertheless, in Europe, the exploration of early school leaving in terms of mental health is yet to mature, and only a few recent studies can be referenced. In France, Huerre and Leroy [6] presented a holistic analysis of school dropout, Brandibas [7] considered truancy to be associated with different types of anxiety, whereas Legleye [8] reported an association between dropout and the progression to daily cannabis use. Jonsson [9] pointed out that Swedish adolescents suffering from depression were less likely than their non-depressed peers to have graduated from higher education.

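### With the stated inputs, 146 participants per group give about 62% power for an odds ratio of 2.0, not 80%; about 219 matched pairs would be needed

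*Protocol article*

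**What the plan says.** The section Sample size calculation sets out all the ingredients. It borrows a European survey figure "to assume a prevalence rate of 13.7% for any psychiatric disorder in the age group 18-24 years". The target is that young adults with a psychiatric diagnosis "have an odds ratio (OR) of at least 2.0 for dropping out of school". It ends: "with alpha error set at 0.05 and statistical power of 80%, 146 participants per group will be needed". It names no formula, sidedness, discordance rate or within-pair correlation.

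The rest of the article fixes the design. Under Recruitment procedure, "There will be one control per dropout who participated in the study", so allocation is 1:1; the five candidate controls requested per case are a reserve against refusal. Control definition specifies individual matching on age, gender, school and grade. Statistical analysis plans McNemar's test for paired proportions and conditional logistic regression, judged at the 5% level. The Background gives a range for the prevalence of at least one DSM IV disorder, from 13.7% to 22.2%.

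**The concern.** The paragraph gives a prevalence, an odds ratio, an error rate, a power and a result, so it can be checked directly, and the result looks too small for an exposure this uncommon. It is the only justification of study size in the article, and it supports the first objective, the comparison of psychiatric disorder between dropouts and controls.

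If 146 is too few, the study claims a power it does not have. A non-significant result from a study described as having 80% power would then carry more weight against an association than it should. The any-disorder comparison is also the most favourable one for prevalence: the research questions ask about single disorders too, and none of these can be more common than any disorder.

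**Working it through.** **Inputs.** From Sample size calculation: control exposure p0 = 0.137, odds ratio ψ = 2.0, alpha 0.05, power 0.80, stated n = 146 per group. From Recruitment procedure: one control per case. Assumed, because the article does not say: a two-sided test (z = 1.960; one-sided 1.645 is tried below), z for power = 0.842, 13.7% as the prevalence in controls, and no within-pair correlation of exposure.

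**Exposure in cases.** p1 = ψp0 / (1 − p0 + ψp0) = 0.274 / 1.137 = 0.241.

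**Matched pairs (fits the planned McNemar and conditional logistic analysis).**
- Probability that a discordant pair has the case exposed: P = ψ/(1 + ψ) = 2/3.
- Discordant pairs needed: m = (1.960/2 + 0.842·√(P(1 − P)))² / (P − ½)² = (0.980 + 0.842 × 0.471)² / (1/6)² = 68.2.
- Probability that a pair is discordant: 0.137 × 0.759 + 0.241 × 0.863 = 0.312.
- Pairs needed: 68.2 / 0.312 = 218.7, so **219**.

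**Unmatched two proportions.** The pooled formula gives 221.3, so 222 per group (241 with continuity correction). The unpooled and arcsine formulas give 219, the log odds ratio formula 228, and a McNemar sample-size formula 225.

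**Power at 146 pairs.** Expected discordant pairs: 146 × 0.312 = 45.5. Then z = (√45.5 × 1/6 − 0.980) / 0.471 = 0.307, a power of **62.1%**. The unmatched formula gives 62.3%, and exact enumeration of the score McNemar test gives 62.2%.

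**Attempts to reproduce 146.**

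| Reading | Needed per group | Power at 146 |
|---|---|---|
| As stated, two-sided | 219 to 241 | about 62% |
| As stated, one-sided | 172 to 193 | about 74% |
| 13.7% as overall prevalence, two-sided | 290 | – |
| 13.7% as prevalence in cases, two-sided | 366 | – |
| Control prevalence 22.2%, two-sided | 161 pairs, 162 unmatched | 76% |
| 2.0 as a prevalence ratio (13.7% v 27.4%), two-sided | 136, or 150 with continuity correction | 83% (uncorrected) |
| Four controls per case | 143 to 145 in the smaller group | – |

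The last two rows come close but contradict the text, which specifies an odds ratio and one control per case. Two changes of input do return 146: a control prevalence of 27.4%, twice the stated figure (145.7), or an odds ratio of about 2.3 at 13.7% (145.4 pairs). Neither is in the article.

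**Detectable odds ratio.** With 146 pairs and 80% power, two-sided: about 2.3 at 13.7% prevalence and about 2.07 at 22.2%.

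**Effect of matching.** If matching cut the share of discordant pairs by 10% or 20%, power at 146 pairs would fall to 57% or 52%. These reductions are illustrative; the article gives no figure for them.

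**The case against.** The arithmetic is not in dispute, but there are fair points about how firmly to state its size.

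- **Sidedness.** Only an alpha of 0.05 is given, and the hypothesis in the Background is directional. A one-sided reading narrows the gap (172 pairs, about 74% power) without closing it. Combining a one-sided test with 22.2% prevalence would need only 53.5 / 0.424 = 126.2, so 127 pairs, and 146 would then suffice. But that changes the stated prevalence and still does not yield 146.
- **Precision.** The 219 belongs to one formula with zero within-pair correlation; two-sided methods range from 219 to 241. It is the low end of that range, and positive correlation would push it up.
- **Origin of 146.** Fisher's exact test of 13.7% against 27.4% with 146 per group has 79.8% power. The authors may have doubled the prevalence, which is an odds ratio of about 2.38, and called it 2.0. That is a plausible guess which the article cannot confirm. Even if right, the stated odds ratio is wrong.
- **True prevalence.** The diagnostic interview covers current, past and lifetime disorders, so exposure may exceed 13.7% and the real shortfall may be smaller. This stands as a caution about the eventual power, but it does not make the stated calculation correct.
- **Importance.** Neither conduct nor analysis has to change. True, but the power claim is still wrong as published.

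**Conclusion.** The concern holds. From the stated inputs, 80% power at a two-sided 5% level requires about 219 matched pairs, and 146 is two thirds of that (146/219 = 0.67). Power for an odds ratio of 2.0 is about 62%, so the chance of missing it is about 38% against the 20% implied. The two-sided level, the reading of 13.7% as control prevalence and the absence of within-pair correlation are assumptions. A one-sided test alone, or 22.2% prevalence alone, shrinks the shortfall but does not remove it, and no combination of inputs stated for the calculation gives 146. The finding does not depend on how 146 arose. It must be corrected because it is the study's only power statement.

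**What to change.** Rewrite the Sample size calculation paragraph.

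1. Use the discordant-pair formula that matches the planned McNemar and conditional logistic analysis, and state the sidedness and the assumed within-pair correlation.
2. Say what 146 pairs deliver: about 62% power for an odds ratio of 2.0 at 13.7% exposure, two-sided 5%, with no within-pair correlation; equivalently, 80% power for an odds ratio of about 2.3 or more.
3. State that an odds ratio of 2.0 would need about 219 pairs under the same assumptions, and more if matching induces positive correlation.
4. If 146 came from an unreported input, such as another prevalence or a doubled prevalence rather than an odds ratio of 2.0, state and justify that input instead.

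The cost is one paragraph and a less favourable power claim. Keeping 146 pairs is acceptable once the claim is corrected; no extra participants are required.
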